### Treatment & sample collection

Patients will receive the following treatment according to national guidelines (Annex II, IV and V) and will be asked to return for follow up:

- **Vivax patients**

CQ (Annex IV) will be administered for three days under direct observation. All patients will be observed for 30 min after drug administration for adverse reactions or vomiting. Any patient who vomits during this observational period will be re-treated with the same dose and observed for an additional 30 min. If the patient vomits the study drug a second time, he or she will receive rescue therapy as defined by the national treatment guidelines (Annex VI).

PQ (Annex V) will be administered unsupervised for 14 days from day 3 – 16.The complete treatment course of PQ will be provided to the patients after completion of schizontocidal treatment. All patients will receive instructions on how to take the drugs and will be asked to return for follow up on, day 6, day 9, day 12, day 16 (at the end of treatment), day 23 and day 30, as well as whenever the patients suffers from signs and symptoms consistent with malaria or an adverse reaction to one of the study drugs. (Annex IX).

- **Falciparum patients:**

AL will be administered twice daily for three days (Annex III). The morning dose will be supervised and the patients given tablets for the evening dose. Whenever supervised treatment is administered, the study patients will be observed for 30 min after drug administration for adverse reactions or vomiting. Any patient who vomits during this observational period will be re-treated with the same dose of medicine and observed for an additional 30 min. If the patient vomits the study drug a second time, he or she will receive rescue therapy (Annex VI). PQ will be given to the patients after schizontocidal treatment is finished and the patients are advised to take the single dose (Annex V) on day 3 unsupervised. All patients will be asked to return for follow up on day 9, day 16, day 23, day 30 and whenever participants suffer from signs and symptoms consistent with malaria or an adverse reaction to one of the study drugs within the follow up period (Annex IX).

- **Patients with mixed infection (Pf and PV):**

AL will be administered twice daily for three days (Annex III). The morning dose will be supervised and the patients given tablets for the evening dose. Whenever supervised treatment is administered, the study patients will be observed for 30 min after drug administration for adverse reactions or vomiting. Any patient who vomits during this observational period will be re-treated with the same dose and observed for an additional 30 min. If the patient vomits the study drug a second time, he or she will receive rescue therapy (Annex VI)

PQ (Annex V) will be administered unsupervised for 14 days from day 3 – 16.The complete treatment course of PQ will be provided to the patients after completion of schizontocidal treatment. All patients will receive instructions on how to take the drugs and will be asked to return for follow up on day 6, day 9, day 12, day 16, day 23, day 30, as well as whenever participants suffer from signs and symptoms consistent with malaria or an adverse reaction to one of the study drugs (Annex IX).

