# Objective

**Primary:**

- To assess side effects observed following unsupervised PQ treatment in *P. vivax* and *P. falciparum* patients

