**Table: Treatment, follow up and sample collection schedule *P.f*, *P. vivax* and mixed infections:**

| **Vivax Patients & Patients with mixed infection** | Day 0 | Day 1 | Day 2 | Day 3 | Day 4 | Day 5 | Day 6 | Day 7 | Day 8 | Day 9 | Day 10 | Day 11 | Day 12 | Day 13 | Day 14 | Day 15 | Day 16 | Day 23 | Day 30 | Un-scheduled visit |
| --- | --- | --- | --- | --- | --- | --- | --- | --- | --- | --- | --- | --- | --- | --- | --- | --- | --- | --- | --- | --- |
| FU P.f. patients | X | X | X | (x) |  |  |  |  |  |  |  |  | X |  |  |  | X | X | X |  |
| FU P.v. patients & mixed | X | X | X | (x) |  |  | X |  |  | X |  |  | X |  |  |  | X | X | X |  |
| Consent | X |  | X |  |  |  |  |  |  |  |  |  |  |  |  |  |  |  |  |  |
| Urinary Pregnancy testing (females, 13- 49years) | X |  |  |  |  |  |  |  |  |  |  |  |  |  |  |  |  |  |  |  |
| Capillary Finger Prick | X | X | X |  |  |  |  |  |  | X |  |  |  |  |  |  | X | X | X | X |
| Venous Blood Sample | X |  |  |  |  |  |  |  |  |  |  |  |  |  |  |  |  |  |  | X* |
| Microscopy | X | X | X | (X) |  |  | X |  |  | X |  |  | X |  |  |  | X | X | X | X |
| Hb | X | X | X | (X) |  |  | X |  |  | X |  |  | X |  |  |  | X | X** | X** | X |
| ACT treatment Pf and Pf/Pv | X | X | X |  |  |  |  |  |  |  |  |  |  |  |  |  |  |  |  |  |
| PQ treatment Pf |  |  |  | X |  |  |  |  |  |  |  |  |  |  |  |  |  |  |  |  |
| CQ treatment Pv | X | X | X |  |  |  |  |  |  |  |  |  |  |  |  |  |  |  |  |  |
| PQ treatment Pf and Pf/Pv |  |  |  | X | X | X | X | X | X | X | X | X | X | X | X | X | X |  |  |  |
| Masimo*** |  |  |  |  |  |  |  |  |  |  |  |  |  |  |  |  | X** |  |  | X |
| Pill count |  |  |  |  |  |  |  |  |  |  |  |  |  |  |  |  | X** |  |  |  |
| AE monitoring  *in case of recurrent parasitaemia  ** in Pv and Pf/Pv patients only  ***only in adults and children >2 yearsX | X | X | X |  |  |  |  |  |  | X |  |  |  |  |  |  | X | X | X | X |

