## Other Endpoints

- Proportion of patients adhering to 14 days of primaquine treatment in the vivax cohort as measured by Masimo and pill count
- Distribution of G6PD activity among the study population
- Frequency and type of variants of the G6PD gene within the study population

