# Sample Size

In 2013 a total of 142 vivax cases and 2190 falciparum cases were registered within the district of Alikadam with the majority of cases occurring during and after the monsoon season. The study hospital treated a total of 49 vivax cases and 432 falciparum cases in the same year. As the proposed study will be conducted during the peak malaria season we propose an enrolment target of approximately 50 vivax cases and 160 falciparum cases.

This study is part of a framework of comparable studies working with similar tools as proposed herein. Results for the primary objective will be pooled together with results of other sites to provide reliable results.

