**17. G6PD result:** ☐☐.☐ **IU/g Hb**

18. **Schizontocidal Treatment**

| Schizontocidal treatment | Pf | Pv | mixed |
| --- | --- | --- | --- |
| 1^st^ Dose (observed) | AL given  ☐ Yes ☐ No ☐  Dose:___________ | CQ given  ☐ Yes ☐ No ☐  Dose:___________ | AL given  ☐ Yes ☐ No ☐  Dose:___________ |
| 2^nd^ Dose | AL given  ☐ Yes ☐ No ☐  Dose:___________ | N/A | AL given  ☐ Yes ☐ No ☐  Dose:___________ |
|  | Was this dose given as observed treatment  ☐yes ☐no |  | Was this dose given as observed treatment  ☐yes ☐no |

19. **Primaquine treatment**

| Primaquine treatment | Pf | Pv | mixed |
| --- | --- | --- | --- |
|  | PQ single dose provided tp patient  ☐ Yes ☐ No ☐  Dose:___________ | PQ full course provided to patient  ☐ Yes ☐ No ☐  Dose:___________ | PQ full course provided to patient  ☐ Yes ☐ No ☐  Dose:___________ |

**Day – 6: Date of visit:** ☐☐-☐☐-☐☐☐☐

20. **Temperature:** ☐☐.☐˚C

21. **Finger prick collected?** ☐ Yes ☐ No

*If yes:* **Blood slide collected?** ☐ Yes ☐ No

*If yes:* Time: ☐☐:☐☐ in 24:00 format (e.g. 4pm is 16:00)

**Parasite count** ________/500RBC or ___________/200WBC

Diagnosis: ☐ Pf ☐ Pv ☐Mixed ☐neg

*If yes:* **Hemoglobin measured?** ☐ Yes ☐ No

*if Yes:* ☐☐.☐ g/dl

**Day – 9: Date of visit:** ☐☐-☐☐-☐☐☐☐

22. **Temperature:** ☐☐.☐˚C

23. **Finger prick collected?** ☐ Yes ☐ No

*If yes:* **Blood slide collected?** ☐ Yes ☐ No

*If yes:* Time: ☐☐:☐☐ in 24:00 format (e.g. 4pm is 16:00)

**Parasite count:** ________/500RBC or ___________/200WBC

Diagnosis: ☐ Pf ☐ Pv ☐Mixed ☐neg

*If yes:* **Hemoglobin measured?** ☐ Yes ☐ No

*if Yes:* ☐☐.☐ g/dl

**Day – 12: Date of visit:** ☐☐-☐☐-☐☐☐☐

24. **Temperature:** ☐☐.☐˚C

25. **Finger prick collected?** ☐ Yes ☐ No

*If yes:* **Blood slide collected?** ☐ Yes ☐ No

*If yes:* Time: ☐☐:☐☐ in 24:00 format (e.g. 4pm is 16:00)

**Parasite count :** ________/500RBC or ___________/200WBC

Diagnosis: ☐ Pf ☐ Pv ☐Mixed ☐neg

*If yes:* **Hemoglobin measured?** ☐ Yes ☐ No

*if Yes:* ☐☐.☐ g/dl

**Day – 16: Date of visit:** ☐☐-☐☐-☐☐☐☐

26. **Temperature:** ☐☐.☐˚C

27. **Finger prick collected?** ☐ Yes ☐ No

*If yes:* **Blood slide collected?** ☐ Yes ☐ No

*If yes:* Time: ☐☐:☐☐ in 24:00 format (e.g. 4pm is 16:00)

**Parasite count :** ________/500RBC or ___________/200WBC

Diagnosis: ☐ Pf ☐ Pv ☐Mixed ☐neg

*If yes:* **Hemoglobin measured?** ☐ Yes ☐ No

*if Yes:* ☐☐.☐ g/dl

28. **Meth hemoglobin measured (only Pf/Pv and Pv patients > 2 years)?** ☐ Yes ☐ No

*if Yes:* ☐☐.☐ in %

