29. **# of days PQ tablets taken:** ___________________________________________

30**. Remaining tablets:** _____________________________________________ ☐Don’t known

**Day – 23: Date of visit:** ☐☐-☐☐-☐☐☐☐

24. **Temperature:** ☐☐.☐˚C

25. **Finger prick collected?** ☐ Yes ☐ No

*If yes:* **Blood slide collected?** ☐ Yes ☐ No

*If yes:* Time: ☐☐:☐☐ in 24:00 format (e.g. 4pm is 16:00)

**Parasite count :** ________/500RBC or ___________/200WBC

Diagnosis: ☐ Pf ☐ Pv ☐Mixed ☐neg

*If yes:* **Hemoglobin measured?** ☐ Yes ☐ No

*if Yes:* ☐☐.☐ g/dl

**Day – 30: Date of visit:** ☐☐-☐☐-☐☐☐☐

24. **Temperature:** ☐☐.☐˚C

25. **Finger prick collected?** ☐ Yes ☐ No

*If yes:* **Blood slide collected?** ☐ Yes ☐ No

*If yes:* Time: ☐☐:☐☐ in 24:00 format (e.g. 4pm is 16:00)

**Parasite count :** ________/500RBC or ___________/200WBC

Diagnosis: ☐ Pf ☐ Pv ☐Mixed ☐neg

*If yes:* **Hemoglobin measured?** ☐ Yes ☐ No

*if Yes:* ☐☐.☐ g/dl

**1^st^ Unscheduled visit: Date of visit:** ☐☐-☐☐-☐☐☐☐

31. **Temperature:** ☐☐.☐˚C

32. **Finger prick collected?** ☐ Yes ☐ No

*If yes:* **Blood slide collected?** ☐ Yes ☐ No

*If yes:* Time: ☐☐:☐☐ in 24:00 format (e.g. 4pm is 16:00)

**Parasite count :** ________/500RBC or ___________/200WBC

Diagnosis: ☐ Pf ☐ Pv ☐Mixed ☐neg

*If yes:* **Hemoglobin measured?** ☐ Yes ☐ No

*if Yes:* ☐☐.☐ g/dl

33. **Meth hemoglobin measured (only Pf/Pv and Pv patients > 2 years)?** ☐ Yes ☐ No

*if Yes:* ☐☐.☐ in %

**2^nd^ Unscheduled visit: Date of visit:** ☐☐-☐☐-☐☐☐☐

34. **Temperature:** ☐☐.☐˚C

35. **Finger prick collected?** ☐ Yes ☐ No

*If yes:* **Blood slide collected?** ☐ Yes ☐ No

*If yes:* Time: ☐☐:☐☐ in 24:00 format (e.g. 4pm is 16:00)

**Parasite count :** ________/500RBC or ___________/200WBC

Diagnosis: ☐ Pf ☐ Pv ☐Mixed ☐neg

*If yes:* **Hemoglobin measured?** ☐ Yes ☐ No

*if Yes:* ☐☐.☐ g/dl

36. **Meth hemoglobin measured (only Pf/Pv and Pv patients > 2 years)?** ☐ Yes ☐ No

*if Yes:* ☐☐.☐ in %

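### For falciparum patients the date of the unsupervised primaquine dose is captured nowhere, and the protocol contradicts itself on whether intake is checked at all

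*Protocol*

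**What the plan says.** The primary objective is "To assess side effects observed following unsupervised PQ treatment in *P. vivax* and *P. falciparum* patients", so falciparum exposure is part of the main question. The Sample Size section sets the numbers: "we propose an enrolment target of approximately 50 vivax cases and 160 falciparum cases".

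Under Treatment & sample collection, falciparum patients receive the tablets once artemether-lumefantrine is finished, and "the patients are advised to take the single dose (Annex V) on day 3 unsupervised". The only PQ entry for them on the day-2 page of the CRF (Annex IX, item 19) is "PQ single dose provided tp patient", with the dose.

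Exposure checks are described in several places:
- The Study Procedures text plans a day-16 pill count where feasible. It names no species, and the same paragraph has just described both the one-dose and the 14-dose arms.
- The schedule table marks pill count and Masimo on day 16 with a footnote: "in Pv and Pf/Pv patients only".
- On the day-16 CRF page, item 28 is restricted by species: "Meth hemoglobin measured (only Pf/Pv and Pv patients > 2 years". Items 29 and 30, the number "of days PQ tablets taken" and the tablets remaining, have no such restriction.
- The only adherence endpoint is "Proportion of patients adhering to 14 days of primaquine treatment in the vivax cohort as measured by Masimo and pill count".

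**The concern.** The drug whose side effects are under study is taken at home, on a date that no one writes down. For the 14-day course there is at least a planned adherence endpoint, with methaemoglobin and a tablet count behind it. For the single dose there is neither an endpoint nor a methaemoglobin check, and the tablet count is planned in one part of the protocol and excluded in another.

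Two things are at stake:
- **Timing.** The symptom form asks for the onset date of each event and its relation to PQ. Without a dose date, an event on day 4 or 5 cannot be placed before or after the drug. The same holds for a fall in haemoglobin (Hb) by day 9.
- **Interpretation of a reassuring result.** A low rate of PQ-caused events could mean that the dose was tolerated or that some patients did not take it. The gametocytaemia endpoint in falciparum patients has the same ambiguity.

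These are data-capture questions. No analysis plan can recover a date that was never collected.

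**Working it through.** The protocol offers no calculation to reproduce here, so the check is mainly a comparison of its parts.

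**Step 1. What each source yields for a falciparum patient**

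| Source | Dose taken? | Date taken? |
|---|---|---|
| CRF day 2, item 19 | No (provision and dose only) | No |
| Study Procedures text, day-16 pill count | Yes, where feasible | No |
| Schedule table, pill count and Masimo | No (vivax and mixed only) | No |
| CRF day 16, item 28 (methaemoglobin) | No (vivax and mixed only) | No |
| CRF day 16, items 29–30 | Yes, if filled in | No |
| Adherence endpoint | No (vivax cohort, 14 days) | No |
| Symptom form | No (event onset, relatedness and PQ stopped only) | No |

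The date column is empty throughout, and the CRF has no day-3 page. The middle column is contradictory: two sources allow a record of intake, while the schedule excludes the pill count. Where a record is made, it comes 16 − 3 = 13 days after the advised dose.

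**Step 2. Why the date matters for Hb**

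If the dose is taken on day 3 as advised, the day-9 Hb lies 9 − 3 = 6 days after it. If it is taken on day 8, the gap is 9 − 8 = 1 day. If it is never taken, there is no exposure. Without an intake date, the first two cases look the same in the data. If the schedule footnote is followed, so does the third.

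**Step 3. Share of enrolment concerned**

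160 / (160 + 50) = 160/210 = 76.2%. Mixed infections have no target. At the 2013 Alikadam ratio there would be about 210 × 26/(2190 + 142) ≈ 2, giving 160/212 = 75.5%. This is a share of target enrolment, not of PQ recipients. The proportion with severe G6PD deficiency is not stated. If it were 5, 10 or 20% (assumption), 152, 144 or 128 falciparum patients would receive the dose.

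**Step 4. Illustration of dilution**

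The protocol gives no intake figure, so *a* below is assumed. For PQ-caused events only, risk among all given tablets = *a* × risk among takers. The upper limit with zero events (exact, one-sided 97.5%) is 1 − 0.025^(1/n). All 160 are taken as given tablets.

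| Assumed intake *a* | Takers, n = 160*a* | A 5.0% risk in takers appears as | Upper limit among takers, zero events |
|---|---|---|---|
| 100% | 160 | 5.0% | 2.3% |
| 90% | 144 | 4.5% | 2.5% |
| 80% | 128 | 4.0% | 2.8% |
| 70% | 112 | 3.5% | 3.2% |
| 50% | 80 | 2.5% | 4.5% |

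The protocol plans no such limit. The table shows only what cannot be known without intake data.

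**The case against.** The strongest reply is that the study sets out to observe side effects arising under current national guidelines, with PQ taken unsupervised. Imperfect intake is then part of what is being observed, and a proportion among all patients given tablets is a legitimate as-prescribed estimate. This stands. It is not a biased answer to the stated objective; it becomes too low only if read as the risk per dose swallowed.

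A reader might go further and infer that nothing records whether falciparum patients took the dose, so that the safety result for 76% of the cohort describes only tablets handed out. The documents do not support that. CRF items 29 and 30 carry no species limit, although item 28 just above them does, and the Study Procedures text is also unrestricted. Falciparum patients attend on day 16. For a single dose, zero or one day taken would answer the question of whether.

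Three further points stand:
- The protocol does not say that non-takers will be analysed as exposed; analysis sets may be defined in an analysis plan not at hand.
- The safety endpoints also count events due to malaria and other drugs, so the overall proportions do not shrink by the factor *a*.
- The planned relative risk of an Hb drop above 25% by G6PD activity is confined to participants on 14 days of PQ, so the falciparum gap does not touch it.

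Relatedness to PQ is recorded for each event, and site staff may well ask about intake when judging it. That does not put a dose date in the database.

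**Conclusion.** The point holds in a limited form. The date of the falciparum dose is captured nowhere, and the Study Procedures text, the schedule footnote and CRF items 29–30 disagree on whether intake is checked. It concerns up to about 160 of 210 target patients, fewer once those with severe G6PD deficiency are left without PQ.

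The consequence depends on which instruction a site follows. Under the schedule, there would be no intake data for these patients. Under the text and CRF, there would be an undated tablet count or recall 13 days after the advised dose. Either way, events and Hb falls cannot be placed relative to the dose. Under the schedule, a low event rate also cannot be separated from non-intake.

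The as-provided proportion stays valid as a description of routine practice. The dilution figures rest wholly on assumed intake, apply only to PQ-caused events, and should not be quoted as an estimate of bias.

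**What to change.** 1. Reconcile the Study Procedures text, the schedule footnote and CRF items 29–30 so that all three say intake is checked in falciparum patients.
2. On the CRF page for their first scheduled visit after day 3, add: dose taken (yes/no), date taken, number of tablets taken, vomited after the dose (yes/no). The treatment text puts that visit on day 9, while the schedule's falciparum row, as it reads here, marks day 12. Settle this at the same time.
3. Record the PQ start date for vivax and mixed patients in the same way.
4. Report falciparum safety proportions for confirmed takers alongside all patients given tablets, and time events from the recorded date. This reporting rule can sit in the analysis plan; the data capture cannot wait for it.

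The cost is a few CRF fields at an existing visit, one corrected footnote and one extra row in the safety tables. The small downside is that intake is self-reported. No dose or clinical rule changes.

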| **Study design** | This study is a prospective observational cohort study actively monitoring the hematologic response, safety and tolerability of routine treatment of *P. falciparum, P. vivax* and mixed malaria infections (*P. falciparum + P. vivax*). The study will be conducted in Alikadam in the Chittagong Hill Tracts (CHT). |
| **Duration of administration** | - *P. falciparum*: supervised AL for 3 days + single dose PQ - *P. vivax*: Supervised CQ for 3 days + unsupervised PQ for 14 days - Mixed infections: supervised AL for 3 days + unsupervised PQ for 14 days |
| **Duration of patient enrolment** | - Six months |
| **Endpoints** | Safety Endpoints:   - Proportion of patients with severe anaemia (Hb<7g/dl) - Proportion of patients receiving blood transfusion - Fractional change in Hb between baseline and day 9,16, 23 and 30 (incl. proportion of patients with >25% drop in Hb between the timepoints) - Proportion of patients with anaemia less than 8g/dl on day 3 and day 9 - Proportion of patients with adverse and serious adverse events   Efficacy endpoints:   - Proportion of patients with any parasitemia on day 1, 2 and 3 after treatment - Proportion of patients with fever on day 1, 2 and 3 after treatment - Recurrence of parasitaemia within 30 days of follow up   Other Endpoints:   - Proportion of patients adhering to 14 days of primaquine treatment in the vivax cohort as measured by Masimo and pill count - Distribution of G6PD activity among the study population - Frequency and type of variants of the G6PD gene within the study population |
| **Date of first patient enrolled** |  |

Contents

[1. Background 5](#_Toc395861878)

[1.1. Local malaria epidemiology and treatment guidelines 5](#_Toc395861879)

[1.2. Study Site 7](#_Toc395861880)

[**1.3.** **Context of project** 9](#_Toc395861881)

[2. Rationale and Aim 9](#_Toc395861882)

[3. Objective 9](#_Toc395861883)

[4. Methods 10](#_Toc395861884)

[4.1. Study Design 10](#_Toc395861885)

[4.2. Inclusion Criteria 10](#_Toc395861886)

[4.3. Exclusion Criteria 10](#_Toc395861887)

[4.4. Study Procedures 11](#_Toc395861888)

[4.4.1. Treatment & sample collection 11](#_Toc395861889)

[4.4.2. Concomitant treatment 15](#_Toc395861890)

[4.4.3. Rescue treatment 15](#_Toc395861891)

[4.4.4. Loss to follow up 15](#_Toc395861892)

[4.4.5. Patient withdrawal and protocol violation 15](#_Toc395861893)

[4.5. Laboratory and test procedures 16](#_Toc395861894)

[4.5.1. Microscopy 16](#_Toc395861895)

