**Table: Maximum amount of venous blood collected on d0 / body weight**

| **Patient’s approximate weight in kilograms** | **Amount (mL)** |
| --- | --- |
| >6 to 7 | 4-5 |
| >7 | 5 |

All participants will be followed daily until day 2 to provide supervised treatment and ensure clinical and parasitological recovery following chloroquine (Pv arm) or artemether-lumefantrine (Pf arm and Pf/Pv arm) treatment.

Thereafter patients (excluding those with severe G6PD deficiency) will be given unsupervised primaquine for 1 dose (Pf arm) or 14 doses (Pv/mix arm) and reviewed again after 7 days (day 9), 14 days (day 16), 21 days (day 23) and 28 days (day 30). All P. vivax and mixed infections will in addition be followed up after 3 and 10 days (day 6 and 12 respectively) to assure the safety of the provided treatment. Any patient developing signs and symptoms indicative of a malarial episode or an adverse event within the follow up period will be asked to re-attend the clinic for an unscheduled visit, where they will be offered clinical management according to local clinic guidelines. A fingerprick will be performed during every follow up and unscheduled visit, 5ml of blood will be collected for every recurring malaria episode (see table below). Information on adverse events will be collected during every visit. Whenever possible a pill count will be performed on day 16.

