# Assessment of variables and statistical methodology

## Safety endpoints

- Proportion of patients with severe anaemia (Hb<7g/dl)
- Proportion of patients receiving blood transfusion
- Fractional change in Hb between baseline and day 6, 9,12,16, 23 and 30 (incl. proportion of patients with >25% drop in Hb between the timepoints)
- Proportion of patients with anaemia less than 7g/dl on day 3 and day 9
- Proportion of patients with adverse and serious adverse events

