# Statistical analyses

- Safety data will be presented as summary statistics (including number, mean, median, interquartile range, standard deviation, minimum and maximum) of all vital signs variables (values and changes from baseline) will be calculated for each visit by treatment group.
- G6PD activity will be categorised and the relative risk (RR) of a drop of Hb > 25% between day 3 and 9 and day 3 and 16 and day 23 and 30 will be calculated per category for all participants treated with 14 days of PQ.
- Hematological results will be presented as continuous variable of Hb concentration at Day 0, 3, 6, 9, 12 and 16. The fractional fall in Hb between baseline and day 9 and 16, will be calculated, as well as the proportion of patients with anaemia less than 7g/dl between day 3 and day 9.
- Parasite clearance rate will be defined according to the World Wide Antimalarial Resistance Network guidelines (WWARN)[[20](#_ENREF_20)]. The parasite clearance time (PCT) is defined as the time elapsed between the patient’s first dose and the time of the first negative blood slide.
- G6PD variants detected will be presented descriptively, G6PD activity observed will be displayed in the form of a histogram displaying G6PD activity vs. number of patients.

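### The schedule table marks the P. falciparum visit on day 12 and leaves day 9 blank, against the text, and omits AE and finger-prick marks on days 6 and 12

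*Protocol*

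**What the plan says.** **Visit days in the text.** Section 4.4 (Study Procedures) says that patients, once given primaquine (PQ), are "reviewed again after 7 days (day 9), 14 days (day 16), 21 days (day 23) and 28 days (day 30"). It then adds two visits for some of them: "All P. vivax and mixed infections will in addition be followed up after 3 and 10 days (day 6 and 12 respectively"). The Falciparum paragraph of section 4.4.1 repeats the Pf days: "All patients will be asked to return for follow up on day 9, day 16, day 23, day 30".

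**Visit days in the table.** The Pf visit row of the schedule table in section 4.4.1 begins "FU P.f. patients | X | X | X | (x"). Its next mark stands under day 12, followed by days 16, 23 and 30. Day 9 is blank.

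**What is collected.** Section 4.4 states: "Information on adverse events will be collected during every visit". It also calls for a finger prick at each follow-up visit and explains days 6 and 12 as safety visits. Section 4.5.2 (Hemoglobin) ties Hb to baseline and every follow-up visit.

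**Where day 9 is used.** The synopsis lists "Fractional change in Hb between baseline and day 9,16, 23 and 30". Section 5.1 has "Proportion of patients with anaemia less than 7g/dl on day 3 and day 9". Section 7 says: "The fractional fall in Hb between baseline and day 9 and 16, will be calculated". None of these is limited to Pv patients.

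**The concern.** A schedule table directs conduct: visit calendars and appointment cards are usually drawn from it. The primary objective covers side effects of unsupervised PQ in both Pv and Pf patients, and Pf patients are most of the planned cohort. Day 9 is their first scheduled review after an unsupervised dose. Because Hb is tied to attendance, a Pf visit booked for day 12 instead would leave no Hb at a timepoint that the endpoints and the analysis section name.

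The blank AE cells on days 6 and 12 concern the other group, those on 14 days of PQ. These visits were added for their safety, yet the table asks for no AE information there.

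**Working it through.** **Step 1: do the columns align?** The table has 20 column heads after the label. The Pf row has 20 cells: four marks (days 0 to 3), eight blanks (days 4 to 11), a mark, three blanks, three marks and a final blank. The mark after the eight blanks is the 4 + 8 + 1 = 13th cell, and the 13th head is day 12. The Pv/mixed row below it also has 20 cells and falls on exactly the days in the text. A cell lost in PDF reading is therefore unlikely.

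**Step 2: sources side by side (scheduled days after day 3).**

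| Source | Days |
|---|---|
| Section 4.4 text, all arms | 9, 16, 23, 30 |
| Section 4.4 text, extra for Pv and mixed | 6, 12 |
| Section 4.4.1 text, Pf | 9, 16, 23, 30 |
| Table, Pf visit row | **12**, 16, 23, 30 |
| Table, Pv/mixed visit row | 6, 9, 12, 16, 23, 30 |
| Table, Hb row | 6, 9, 12, 16, 23 and 30 (last two footnoted Pv and mixed only) |
| Table, microscopy row | 6, 9, 12, 16, 23, 30 |
| Table, finger-prick row | 9, 16, 23, 30 |
| Table, AE row | 9, 16, 23, 30 |

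The two text sources agree with each other and reserve day 12 for Pv and mixed patients. The Hb, microscopy, finger-prick and AE rows all mark day 9 with no species footnote, and the last two are blank on day 12. The Pf visit row stands alone.

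**Step 3: size if Pf visits were booked from that row.**
- Patients: section 8 targets about 160 Pf and 50 Pv cases, so 160 / (160 + 50) = 160/210 = 76%. No target is given for mixed infections. The 160 is an upper bound, because severely G6PD-deficient patients receive no PQ.
- Synopsis Hb-change days {9, 16, 23, 30}: all 4 fall on Pf visits under the text, and 3 of 4 under the row.
- Section 5.1 Hb-change days {6, 9, 12, 16, 23, 30}: 4 of 6 under the text (9, 16, 23, 30) and 4 of 6 under the row (12, 16, 23, 30). The loss is day 9 itself, not the number of readings.
- Section 7 fractional fall, days {9, 16}: 2 of 2 under the text, 1 of 2 under the row.
- First scheduled review after the day-3 dose: 9 − 3 = 6 days under the text, 12 − 3 = 9 days under the row. (The 7 days in section 4.4 count from day 2.)

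**Step 4: AE marks in the 14-day PQ group.** Pv and mixed visits from day 6 to day 16 fall on days 6, 9, 12 and 16. AE and finger prick are marked on 2 of these 4 (days 9 and 16). Hb and microscopy are marked on all 4.

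**Step 5: Hb on days 23 and 30.** The table footnote limits these to Pv and mixed patients. The synopsis, section 4.5.2 and section 5.1 carry no such limit. Section 7 uses days 23 and 30 only in the relative-risk analysis, which is restricted to patients on 14 days of PQ.

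**The case against.** The strongest reply is that nobody need be misled. Only one row lacks day 9, the text gives day 9 twice, and other rows mark procedures on that day. There is one study centre, with on-site training and weekly contact with staff. This stands, and it makes the loss of the day-9 Hb a risk and not a forecast. It does not make the row right.

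The practical harm is also limited. Pf patients would still have Hb on days 12 and 16 and are told to return for any adverse reaction. The relative-risk analysis by G6PD category excludes patients given single-dose PQ. The symptom form asks for an onset date, so an event missed on day 6 could still be recorded on day 9, though later and from recall.

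It might be said that the day-9 procedure marks serve only Pv and mixed patients, since the head of the table's first column names just those groups. But the caption covers all three infections, Pf has its own rows, and a footnote restricting single cells to Pv and mixed would be redundant if the whole table were so restricted.

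Two stronger readings are tempting:
- A reader might infer from the case record form, which has Hb fields open to all species on days 9, 23 and 30, that it proves the intended schedule. It does not. Its day-6 and day-12 pages are equally open, although those visits are for Pv and mixed patients only.
- A reader might infer that the footnote on days 23 and 30 is a plain mistake. The documents do not show that. Section 7 uses those days only for the 14-day PQ group, which is the group the footnote selects, so the limit may be intended.

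**Conclusion.** The contradiction is certain; its effect is conditional. The Pf visit mark is on the wrong day, and the two text sections settle that day 9 is meant. If Pf visits were scheduled from that row, up to about 160 of 210 patients (76%) would lose the day-9 Hb, and their first review after the dose would come at 9 days instead of 6. This assumes that the row, not the text, drives booking, and that enrolment meets its target.

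The missing AE and finger-prick marks on days 6 and 12 are a second definite error, because section 4.4 requires both at those visits. The footnote on Hb for days 23 and 30 is a mismatch with the endpoint text, and either side could be the one to change. The point is modest but worth correcting, since it touches a named safety timepoint in most of the cohort.

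**What to change.** 1. In the Pf visit row, move the mark from day 12 to day 9. The row then reads 0, 1, 2, (3), 9, 16, 23, 30 and agrees with sections 4.4 and 4.4.1.
2. Mark AE monitoring and finger prick on days 6 and 12.
3. Decide whether Pf patients have Hb on days 23 and 30. Either remove the footnote from those two Hb cells, or restrict the synopsis, section 4.5.2 and section 5.1 to Pv and mixed patients on those days.
4. As a clerical correction, relabel the day 3 to 16 PQ row, which names Pf and mixed where Pv and mixed is meant.

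The cost is a corrected table, with no visits beyond those in the text and no new Hb fields on the case record form. If the footnote is removed, the table gains at most 2 Hb readings per Pf patient, 2 × 160 = 320 in all, at visits where a finger prick is already marked. If the endpoint text is restricted instead, it gains none.
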